### Study outline

#### Randomization

The investigator will verify the eligibility of the patient with respect to the inclusion and non-inclusion criteria. After the delivery of oral information regarding the study, written consent will be collected (day of inclusion). Both strategies will be explained to the patients before enrollment in the study, along with their pros and cons. For the preregistration evaluation, the included patients will undergo a standard preoperative work-up, as per local protocol. Randomization will be performed by a computer on at least the day before surgery, and the results of the randomization will be given to the patient on at least the day before surgery. All the explanations related to the content of the strategy will again be explained to the patient.

#### Intervention

An anesthesia consultation is planned before the surgery according to the habits of each department. Participation in the study will not alter the anesthetic procedures. The technical modalities of IPAA are not restricted, but it is mandatory that these modalities are identical in both groups for each center in terms of the type of approach (laparoscopic, single-port, robotic), type of anastomosis (hand-sewn or stapled), pelvic drainage and pouch drainage. Open surgery can be the chosen surgical approach for some patients, provided that a mini-invasive approach cannot be performed due to the surgical history or medical contra-indications, as estimated by the surgeon in charge. A J-pouch will be mandatory as it is the pouch of reference [18].

The defunctioning ileostomy is a covering loop ileostomy, which can be fashioned either in the right or left iliac fossa. The use of an ostomy rod is not mandatory and left to the surgeon’s judgment. Ileostomy closure will be performed 6 to 12 weeks after IPAA as per local protocol or later in case of pelvic sepsis. During stoma closure, the type of ileo-ileal anastomosis (whether end-to-end or side-to-side, hand-sewn or stapled) is not restricted. A CT enema scan can be performed before ileostomy closure to assess the absence of anastomotic leakages, as per the local protocol.

The patients randomized in the experimental group will be treated by completion proctectomy and the creation of an IPAA without a defunctioning ileostomy, which corresponds to a modified two-stage IPAA. As defunctioning ileostomy is omitted in this group, an anastomotic leakage test can be performed when deemed necessary by the surgeon in charge. However, the anastomotic leakage test will not be mandatory.

No concomitant care and interventions are prohibited during the trial.

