## Methods and design

The IDEAL trial is a nationwide prospective, multicenter, open-label, randomized controlled trial in which IBD patients scheduled for completion proctectomy and IPAA will be randomized between having a defunctioning ileostomy (the ‘ileostomy’ strategy) and not having a defunctioning ileostomy (the ‘no ileostomy’ strategy). The study cannot be blinded because the presence of a stoma cannot be simulated and is obvious to both patients and practitioners. The study duration will be 48 months, and the recruitment duration will be 33 months. The study design is summarized in Fig. 1.

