### Endpoints

The primary endpoint is the 6-month global postoperative morbidity, i.e., the number of patients who develop at least one complication at the 6-month follow-up, encompassing both surgical and medical complications, as well as the morbidity of ileostomy closure. The 6-month timepoint is defined from the completion proctectomy and is therefore the same in both groups. We chose a 6-month endpoint because half of the patients will undergo ileostomy closure 6 to 12 weeks after IPAA. Therefore, a one-month or 3-month endpoint would be too short to correctly assess the morbidity of completion proctectomy +/− ileostomy closure. Moreover, a significant part of morbidity related to defunctioning ileostomy occurred in the long-term (i.e., after 30 days) in previously published studies [7, 8].

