The secondary endpoints are as follows: 6-month major morbidity based on the Clavien-Dindo classification, [14] i.e., number of patients who develop at least one major complication at the 6-month follow-up; 6-month unplanned reoperation rate, i.e., any unplanned abdominal surgery, whether urgent or elective, other than ileostomy closure; 6-month anastomotic leakage rate assessed by a CT scan with an iodine injection, i.e., pelvic abscess, pelvic extradigestive air, pelvic free fluid or pelvic infiltration; 6-month mortality (linked or not with the disease); initial and cumulative 6-month length of hospital stay; 6-month unplanned readmission rate, i.e., other than for ileostomy closure; global and digestive quality of life (QoL) assessed by the Cleveland Global Quality of Life (CGQL) score [15] and the EuroQol Five-levels (EQ-5D-5 L) (i.e., utility values for health states) [16] at baseline and 3 and 12 months from continuity restoration (i.e., either IPAA or ileostomy closure); functional results assessed by the Cleveland Pouch Functional score (PFS) 3 and 12 months from continuity restoration [15]; 12-month pouch results: pouch failure (i.e., with definite ileostomy), anastomotic stricture, pouch in place, and repeat IPAA 12 months from continuity restoration; 12-month global morbidity (i.e., the number of patients who develop at least one complication 12 months from continuity restoration); and 12-month cost-utility analysis, performed 12 months from continuity restoration (cf. *‘* Economic assessment’ below). Though many redo-IPAAs are performed after one year, it is a secondary endpoint and it was felt not relevant enough in this trial to extend its follow-up.

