#### Statistical analysis

A sample size calculation will be performed on the hypothesis formulated on the primary endpoint, i.e., the overall morbidity, assessed 6 months post-randomization. Based on previous reports, the overall 6-month morbidity rate is 30% in the case of no ileostomy creation (i.e., experimental group) vs. 55% otherwise (control group) [6–8, 11–13]. With the alpha risk and power fixed to 0.05 and 0.80, respectively, 88 patients need to be included in each group, or 176 in total [Power Analysis and Sample Size Software Version 2008, Utah, USA]. Considering a drop-out rate of 10%, the objective is set to 194 patients.

The full analysis population (including all subjects who will be randomized and will at least be evaluated at baseline) will be used in the primary analysis, and the per-protocol population (including all subjects who will be randomized and will not have major protocol deviations) will be used in the secondary analysis to assess the robustness of the results. The demographic and baseline characteristics will be summarized for the 2 groups (‘control’ and ‘experimental’ groups). The scores of the QoL questionnaires will be calculated from the algorithm provided by the authors of the tools. No comparisons will be provided in accordance with the CONSORT guidelines.

The primary endpoint will be compared between the 2 groups (χ^2^ test or Fisher’s exact test) for the primary analysis. Logistic regression will be performed to adjust for potential confounding factors; variables relevant to the models will be selected based on their clinical interest and/or a threshold *p*-value ≤0.1 during univariate analysis. The final models will express the odd ratios and their 95% confidence intervals. The unadjusted analysis will be the primary analysis, and the adjusted analysis will be a complementary analysis. For the secondary endpoints, quantitative data will be compared using the Student’s t test or Mann-Whitney U test in accordance with the variable distribution, whereas qualitative data will be compared using χ^2^test or Fisher’s exact test, as appropriate.

For the analysis of overall survival, the last date of known contact will be used for subjects who have not died (the subjects will be considered censored). Overall survival will be estimated according to the Kaplan-Meier method. Comparisons between the 2 groups will be performed with the log rank test for the Kaplan-Meier estimates. Cox models will be created.

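### A routine pre-closure CT enema is open only to control patients, so symptom-free leaks, defined by CT signs alone, will be found preferentially in the control arm.

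*Protocol article*

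**What the plan says.** All references are to the protocol article.

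- **Intervention.** "A CT enema scan can be performed before ileostomy closure to assess the absence of anastomotic leakages, as per the local protocol". Closure is planned 6 to 12 weeks after the pouch operation, later if there is pelvic sepsis. For the experimental arm, the same section allows a leak test at the surgeon's discretion, says it is not mandatory, and gives neither its method nor its timing.
- **Endpoints, secondary.** The leak endpoint is the "6-month anastomotic leakage rate assessed by a CT scan with an iodine injection". The signs listed are pelvic abscess, air outside the bowel, free fluid or infiltration. Neither symptoms nor a treatment consequence is required.
- **Endpoints, primary.** The primary endpoint is "the number of patients who develop at least one complication at the 6-month follow-up", covering surgical and medical complications and the morbidity of closure, counted from proctectomy in both arms.
- **Discussion.** The 6-month horizon is defended partly because it captures late leaks, and the leak rate without a stoma is called a major concern.
- **Data collection and monitoring.** The scheduled follow-up visits are clinical reviews. No imaging visit is named.
- **Methods and design.** "The study cannot be blinded".

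**The concern.** When an outcome is defined by what a scan shows, the arm that is scanned more often will show more of it, even if the true rates are equal. The pre-closure CT enema is a screening look for leaks tied to an event that only control patients have. A symptom-free collection or some pelvic fluid seen on it meets the leak definition. The same finding in an experimental patient without symptoms may never be seen.

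The extra findings raise the control rate, which is the direction of the superiority hypothesis. Stratifying randomization by center does not remove the imbalance, because within a center that scans before closure only controls are scanned. The Intervention section requires several technical modalities to be the same in both groups at each center, but that list does not include leak imaging. At stake is the leak comparison, which readers will use to judge the safety of omitting the stoma, and possibly part of the primary result.

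**Working it through.** **Inputs from the article**

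- Planned morbidity: "the overall 6-month morbidity rate is 30% in the case of no ileostomy creation (i.e., experimental group) vs. 55% otherwise (control group").
- Size: "88 patients need to be included in each group, or 176 in total"; 194 after a 10% dropout allowance, so 194 / 2 = 97 per arm.
- Test: χ² or Fisher's exact test, alpha 0.05. Sidedness is not stated; two-sided is assumed here.
- Leak rate for illustration: 17%, from the retrospective comparison in the Background (16.7% with ileostomy, 17.1% without).

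The article gives no figure for silent leaks, so there is none to reproduce. The sample size enters only as the number per arm; how 88 was derived is a separate matter.

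**Assumptions (not in the documents)**

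- u, share of controls who get the routine scan: 0 to 100%, since the scan is optional.
- s, share of scanned patients with a leak sign seen only on that scan: 3% to 8%, taken to be the same in patients with and without another complication.

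**Step 1. Extra control leaks = u × s**

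- u = 0: 0 points
- u = 0.5, s = 0.03: 1.5 points
- u = 1, s = 0.08: 8 points

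**Step 2. Extra primary-endpoint events = u × s × (1 − p)**

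Here p is control morbidity apart from scan-only findings. Only patients with no other complication can become new events.

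- p = 0.55: at most 1 × 0.08 × 0.45 = 3.6 points
- p = 0.30: at most 1 × 0.08 × 0.70 = 5.6 points
- u = 0: 0 points

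The planned difference is 55 − 30 = 25 points.

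**Step 3. Effect on the leak test**

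Exact two-sided rejection probability of the uncorrected χ² test, from the two binomial distributions, true leak rate 17% in both arms:

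| Observed control rate | Artefact | 97 per arm | 88 per arm |
|---|---|---|---|
| 17% | 0 points | 5.1% | 4.9% |
| 18.5% | 1.5 points | 5.9% | 5.6% |
| 22% | 5 points | 14.3% | 13.2% |

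**Step 4. Effect on the primary test**

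Probability of a false win for no ileostomy with equal true morbidity, 88 per arm:

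| True morbidity | No artefact | Largest artefact (u = 1, s = 0.08) |
|---|---|---|
| 55% | 2.8% | 7.6% (3.6 points) |
| 30% | 2.6% | 12.2% (5.6 points) |

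With half the controls scanned and s = 0.03, the false-win probability is 3.4% at 55% morbidity and 3.6% at 30%.

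**The case against.** Four points can fairly be made.

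1. **A reader might infer that silent leaks are found in one arm only.** The article does not support that. Experimental patients may have the discretionary leak test, and nothing prevents a symptom-driven CT in either arm. The secondary endpoint can also be read as a CT for everyone at 6 months, and a full schedule of assessments may sit in a document not shown. This stands, and the imbalance is one of degree. It does not vanish, though: even with a common 6-month scan, controls would have an extra, earlier look within a cumulative endpoint.

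2. **The link to the primary endpoint is inferred.** The CT definition belongs to the secondary leak endpoint, and the article never says that a symptom-free CT sign is a complication. The Discussion speaks of late leaks, not silent ones. This also stands: the text suggests that leaks count, but the effect on the primary endpoint is conditional.

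3. **The size is assumed.** The scan follows local practice, so the share scanned could be near zero, and a 1.5-point artefact hardly moves the error rate. The 5.6-point figure holds only if control morbidity apart from scan-only findings is about 30%, not the planned 55%. This stands.

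4. **A reader might infer that the asymmetry can hide a leak excess from safety oversight.** It cannot. The committee in the Patient safety section compares the experimental-arm leak rate with a fixed 15% threshold, and extra control scans do not enter that check. What is affected is the between-arm comparison.

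**Conclusion.** The concern holds as preferential detection in the control arm, favouring no ileostomy. It follows from three statements in the article: a leak-screening scan tied to closure, a leak definition based on CT signs alone, and no named counterpart in the experimental arm.

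For the leak endpoint the effect is direct and ranges from nothing to material: 0–8 points on the assumed ranges, with the rejection rate nearly tripled at 5 points. For the primary endpoint it applies only if scan-only findings are counted as complications. It is then modest against the planned 25 points but could matter if the observed difference is much smaller. The scanned share and the scan-only rate are both assumptions, and true sizes outside these ranges are possible.

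**What to change.** - Record in the eCRF the indication for every pelvic CT (routine before closure, or prompted by clinical signs).
- For the between-arm leak comparison and for the primary endpoint, count in both arms the leaks found on imaging or examination prompted by clinical signs.
- Report leaks found only on the routine pre-closure CT enema in a separate table, whether or not they changed management. A clause that counts them when management changed would bring the imbalance back, because a leak seen on that scan can itself delay closure, and only controls have a closure.
- Give a sensitivity analysis of both endpoints with and without these scan-only leaks.

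The cost is one eCRF field and a sentence in each endpoint definition. No scans are added or removed, and the committee's threshold is untouched. The small downside is that silent leaks leave the main count and appear in a separate table, which the with-and-without analysis keeps in view.

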#### Statistical analysis

A sample size calculation will be performed on the hypothesis formulated on the primary endpoint, i.e., the overall morbidity, assessed 6 months post-randomization. Based on previous reports, the overall 6-month morbidity rate is 30% in the case of no ileostomy creation (i.e., experimental group) vs. 55% otherwise (control group) [6–8, 11–13]. With the alpha risk and power fixed to 0.05 and 0.80, respectively, 88 patients need to be included in each group, or 176 in total [Power Analysis and Sample Size Software Version 2008, Utah, USA]. Considering a drop-out rate of 10%, the objective is set to 194 patients.

The full analysis population (including all subjects who will be randomized and will at least be evaluated at baseline) will be used in the primary analysis, and the per-protocol population (including all subjects who will be randomized and will not have major protocol deviations) will be used in the secondary analysis to assess the robustness of the results. The demographic and baseline characteristics will be summarized for the 2 groups (‘control’ and ‘experimental’ groups). The scores of the QoL questionnaires will be calculated from the algorithm provided by the authors of the tools. No comparisons will be provided in accordance with the CONSORT guidelines.

The primary endpoint will be compared between the 2 groups (χ^2^ test or Fisher’s exact test) for the primary analysis. Logistic regression will be performed to adjust for potential confounding factors; variables relevant to the models will be selected based on their clinical interest and/or a threshold *p*-value ≤0.1 during univariate analysis. The final models will express the odd ratios and their 95% confidence intervals. The unadjusted analysis will be the primary analysis, and the adjusted analysis will be a complementary analysis. For the secondary endpoints, quantitative data will be compared using the Student’s t test or Mann-Whitney U test in accordance with the variable distribution, whereas qualitative data will be compared using χ^2^test or Fisher’s exact test, as appropriate.

For the analysis of overall survival, the last date of known contact will be used for subjects who have not died (the subjects will be considered censored). Overall survival will be estimated according to the Kaplan-Meier method. Comparisons between the 2 groups will be performed with the log rank test for the Kaplan-Meier estimates. Cox models will be created.

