**Methods/design:**

This is a multicenter randomized open trial comparing completion proctectomy and IPAA without (experimental) or with (control) DI in patients presenting with ulcerative colitis or indeterminate colitis. Crohn’s disease patients will not be included. The design is a superiority trial. The main objective is to compare the 6-month global postoperative morbidity, encompassing both surgical and medical complications, between the two groups. The morbidity of DI closure will be included, as appropriate. The sample size calculation is based on the hypothesis that the overall 6-month morbidity rate is 30% in the case of no stoma creation (i.e., experimental group) vs. 55% otherwise (control group). With the alpha risk and power are fixed to 0.05 and 0.80, respectively, and considering a dropout rate of 10%, the objective is set to 194 patients. The secondary objectives are to compare both strategies in terms of morbi-mortality at 6 months and functional results as well as quality of life at 12 months, namely, the 6-month major morbidity and unplanned reoperation rates, 6-month anastomotic leakage rate, 6-month mortality, length of hospital stay, 6-month unplanned readmission rate, quality of life assessed 3 and 12 months from continuity restoration (i.e., either IPAA or stoma closure), functional results assessed 3 and 12 months from continuity restoration, 12-month pouch results, 12-month cost-utility analysis, and 12-month global morbidity.

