An old randomized study from 1992 included 45 patients with no corticosteroid treatment and compared systematic ileostomy during IPAA and no ileostomy. Half of the patients in each group had STC, and the postoperative morbidity was 52% in the “ileostomy” group vs. 32% in the “no ileostomy” group (including an SBO incidence of 22% in the “ileostomy” group vs. 9% in the “no ileostomy” group). These differences were not significant, but the number of patients was small, and these results did not take into account the morbidity of ileostomy closure. Moreover, the mean hospital length of stay (LOS) was significantly longer in the “ileostomy” group than in the in the “no ileostomy” group when both IPAA and ileostomy closure were assessed [6].

More recently, some retrospective case-controlled studies have assessed one-stage IPAA (i.e., total proctocolectomy and IPAA without ileostomy) [11, 12]. The morbidity was comparable between patients who underwent one-stage and those who underwent traditional two-stage IPAA. However, the majority of the patients had FAP, not IBD; all IBD patients were carefully selected, and none received corticosteroid medication. Thus, these results cannot be extended to all colonic IBD patients. Interestingly, a retrospective study emanating from international tertiary care centers found that a “modified” two-stage procedure might be the best option for IBD patients who are at high risk for postoperative morbidity [7]. Namely, Sahami et al. compared 305 IBD patients undergoing IPAA with defunctioning ileostomy to 316 patients undergoing IPAA without defunctioning ileostomy. The rate of anastomotic leakage was not influenced by the ileostomy (ileostomy 16.7% vs. no ileostomy 17.1%, *p* = 0.92), but the ileostomy group presented with more SBO in the long term than the no ileostomy group (ileostomy 18.9% vs. no ileostomy 10.3%, *p* = 0.003). Defunctioning ileostomy was an independent risk factor for SBO (OR = 2.58 CI_95%_[1.5–4.7]). Moreover, the risk of pouch failure over time was similar between the two groups in the Kaplan-Meier analysis.

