**Fig. 1 Fig1:**
[figure not shown]
Flow chart of the IDEAL trial *Defunctioning ileostomy, CR: continuity restoration

The list of randomization will be established before the implementation of the study with a 1:1 allocation ratio. It will be elaborated under the responsibility of the Clinical Research Platform, Assistance Publique – Hôpitaux de Marseille (APHM). A computer-generated randomized list will be drawn up using a permuted block design. Two stratification indicators will be retained: the center and the body mass index (< or ≥ 25 kg/m^2^).

This trial is supported by a grant from the French Ministry of Health (PHRC-18_0764).

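### The printed planning inputs (55% vs 30%, alpha 0.05, power 0.80) give 61 to 69 patients per group, not the stated 88

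*Protocol article*

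**What the plan says.** The Statistical analysis section of the protocol article assumes that "the overall 6-month morbidity rate is 30% in the case of no ileostomy creation (i.e., experimental group) vs. 55% otherwise (control group"). From this it concludes: "With the alpha risk and power fixed to 0.05 and 0.80, respectively, 88 patients need to be included in each group", which it totals to 176. It then adds an allowance for loss: "Considering a drop-out rate of 10%, the objective is set to 194 patients". The Methods/design paragraph of the abstract gives the same two rates and the same 194, introduced by "With the alpha risk and power are fixed to 0.05 and 0.80, respectively, and considering a dropout rate of 10" percent.

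The other inputs are plain. Allocation is 1:1, the abstract says "The design is a superiority trial", and the primary analysis is an unadjusted chi-square or Fisher's exact test. The article names the software but not the formula, whether a continuity correction was used, or whether alpha is one- or two-sided. It mentions no interim look, clustering or other inflation that would raise the number before dropout.

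**The concern.** A sample size sentence that prints both event rates, alpha, power and the resulting number can be checked from itself. This one fails the check by a wide margin: 88 is 44% above the pooled answer (88/61 = 1.44) and 28% above the largest standard answer (88/69 = 1.28). At least one printed figure is therefore not the one used.

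Two things are at stake. First, the justification for the number randomised: on the printed inputs 122 to 138 evaluable patients would do (2 × 61 to 2 × 69), yet 176 are required, a gap of 38 to 54 that the text does not explain. Second, how the result is read: a null finding from a trial described as having 80% power for a 25-point difference carries different weight if the power for that difference was really 91% to 93%.

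**Working it through.** **Inputs.** p1 = 0.55 (ileostomy), p2 = 0.30 (no ileostomy), difference d = 0.25, alpha 0.05, power 0.80 and 1:1 allocation, all from the article. Two-sided testing is my assumption; one-sided is also tried.

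**Step 1: try to reproduce 88 at 80% power.** Pooled formula, with mean rate p = 0.425:

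n = [z(alpha) × √(2p(1−p)) + z(power) × √(p1(1−p1) + p2(1−p2))]² / d²

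- √(2 × 0.425 × 0.575) = 0.6991 and √(0.2475 + 0.2100) = 0.6764
- n = (1.960 × 0.6991 + 0.8416 × 0.6764)² / 0.0625 = 1.9395² / 0.0625 = 60.2, so 61

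Continuity correction: n′ = (n/4) × [1 + √(1 + 4/(n × d))]². With n = 60.19 this is 15.05 × (1 + 1.1251)² = 67.95, so 68.

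Other variants at 80% power:

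| Method | Per group |
|---|---|
| Unpooled, two-sided | 58 |
| Arcsine, two-sided | 60 |
| Unpooled with continuity correction, two-sided | 66 |
| Fisher's exact, by enumeration | 69 (79.7% power at 68, 80.4% at 69) |
| Pooled, one-sided 0.05 | 48 |
| Pooled with continuity correction, one-sided 0.05 | 55 |

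None gives 88.

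**Step 2: power that 88 per group delivers for 55% vs 30%.** Exact enumeration, two-sided 0.05:

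- chi-square, uncorrected: 93.1%
- chi-square with continuity correction: 90.9%
- Fisher's exact: 90.9%

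**Step 3: what could have produced 88.**

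- 55% vs 30% at 90% power: pooled n = (1.960 × 0.6991 + 1.2816 × 0.6764)² / 0.0625 = 80.1, so 81. With continuity correction 87.89, so 88.
- 55% vs 33% at 80% power: pooled n = 78.7, so 79. With continuity correction 87.58, so 88.
- 55% vs 34% at 80% power: pooled n = 86.7, so 87, close to 88 without correction. With correction it is 96.01, so 97.

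So at least two sets of inputs round up to exactly 88, and both need a correction that the article does not mention.

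**Step 4: dropout.** 176 × 1.10 = 193.6, so 194, which reproduces the stated total. To keep 176 after 10% loss the divisor form is needed: 176 / 0.90 = 195.6, so 196. With 194 randomised and 10% lost, 174.6 remain, about 87 per group. The loss at which 176 are still left is 1 − 176/194 = 9.3%. Exact chi-square power at 87 per group is 92.8%, against 93.1% at 88.

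**The case against.** The strongest reply is that nothing in the trial's validity depends on this. The endpoint, the primary test and the type I error are unaffected, the trial exceeds its stated power on its own assumptions, and the remedy adds no patients. All of that stands, and it makes this a reporting error rather than a design failure. It does not rescue the sentence: rates, alpha, power and size are printed together and disagree, so no fuller document could make them agree as printed.

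A reader might go further and infer that the trial was really planned at 90% power. The documents do not support that as fact. The match needs pooled variance with continuity correction, which the article does not name; without the correction 90% power needs 81. A control rate of 55% against 33% at the stated 80% power fits 88 just as well.

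A reader might also test the plan against the 1992 randomised study in the Background, which found 52% vs 32%, and call the effect optimistic. That comparison is not like for like. The article says those results left out the morbidity of ileostomy closure, which the IDEAL endpoint counts, and only half of each group had had a subtotal colectomy. The planning rates are also attributed to several references together. A sensitivity line for those rates would be optional.

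Nor do the documents show that the ethics or safety committee was misled. The full protocol that they may have seen is not shown, and the safety review is tied to a leak-rate threshold, not to the power statement.

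**Conclusion.** The sample size statement is wrong as written, in the Statistical analysis section and, through the same rates, power and total, in the abstract. The printed inputs call for 61 to 69 per group with two-sided testing and a pooled, continuity-corrected or Fisher calculation, and fewer with one-sided testing. The stated 88 gives 91% to 93% exact power for 55% vs 30%. The conclusion rests on the printed rates, alpha and power and on 1:1 allocation; two-sidedness is assumed, but one-sided testing only widens the gap. Which figure was misreported cannot be settled from the article.

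The dropout inflation is short by two patients (194 vs 196). One could read this as leaving the trial under-recruited. It does not: the cost is about 0.3 percentage points of power (93.1% to 92.8%), so it deserves a footnote only.

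**What to change.** Keep 194. Retrieve the original software output and correct both places so that power, event rates, sidedness and method agree.

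- If 55% vs 30% stands, replace 0.80 with the power that 88 per group delivers at two-sided 0.05, and name the method: nominally 90% by the continuity-corrected pooled formula, or 91% to 93% by exact calculation, depending on the test.
- If 0.80 was intended, replace the rates with those that 88 was sized for: about 55% vs 33% with continuity correction, or about 55% vs 34% without.
- In a footnote, say that 194 preserves 176 evaluable patients up to 9.3% dropout, or give 196 if 176 must survive a full 10% loss.

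The cost is a few words in the abstract and the Statistical analysis section, and in the SAP if it repeats the statement. No added patients are needed for power; choosing 196 in the footnote would add two.
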